### Intervention

Subjects will be randomised to receive either azithromycin 500 mg three times a week or placebo during a 1-year period. During this year subjects will be followed at the outpatient department at 3, 6, 9 and 12 months after initiating the study. During these visits the following tests will be performed according to the flowchart (Table 1):

Lung function testing

Sputum sample collection

Peripheral blood collection

Throat swab

Rectal swab

DS14 questionnaire for assessment of type D personality (only on day 1 and month 12)

Hospital Anxiety Depression Scale (HADS)

12-Item Short Form Health Survey (SF-12)

St. George’s Respiratory Questionnaire (SGRQ).

**Table 1 T1:** Overview of outpatient department visits and tests

	**Day 1**	**Month 3**	**Month 6**	**Month 9**	**Month 12**	**Other***
Informed consent	X					
Blood works	X	X	X	X	X	X
Microbiology	X	X	X	X	X	X
Lung function testing	X	X	X	X	X	
Rectal swab	X		X		X	
Questionnaires	X	X	X	X	X	X

In case of exacerbation subjects have the choice to get treatment from their general practitioner or to visit the hospital to be seen by the investigator. Either way sputum and peripheral blood will be collected for immunological and microbiological investigations. Also the subjects with an exacerbation will be asked to complete the SF-12, HADS and SGRQ.

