### Secondary study outcome

Measurement of lung function parameters and 6 min walking distance.

Assessment of presence of type D personality by DS14 questionnaire.

Disease specific health related quality of life measured by St. George’s Respiratory Questionnaire (SGRQ).

Generic health status measured by the 12-Item Short Form Health Survey (SF-12).

Indication of anxiety and depression by Hospital Anxiety Depression Scale (HADS).

Microbiology: Sputum specimens will be cultured. Polymerase chain reaction (PCR) in sputum and serology in serum for viral and atypical microorganisms will be performed. The rectal swabs will be tested for change in rectal flora as a result of maintenance azithromycin.

Measurement of inflammatory markers in serum [erythrocyte sedimentation rate (ESR), C-reactive protein (CRP), pro-adrenomedullin, (pro-ADM), interleukin-6 and cytokine profiles of T-helper 1, T-helper 2 and T-helper 17 cells].

Decrease in percentage of clinical versus outpatient department exacerbations.

Difference in treatment effect between subjects with and without steroid maintenance therapy as hypothesis-generating secondary analysis.

Adverse events of treatment. Symptoms that are believed to be (possibly) related to therapy will be reviewed at the outpatient department. If a patient has an adverse event that is thought to be drug related and that does not resolve, then the patient will be withdrawn from the study. There will be no routine ECG screening since azithromycin (in contrast to erythromycin) is much less likely to be a cause of a prolonged QTc interval.

Length of hospital stay.

Time till first exacerbation.

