### Sample size and statistical analysis

#### Power calculation and number of study subjects

This calculation starts with the assumption that the number of exacerbations follows a pure Poisson distribution with a mean rate of 3 per subject per year in the placebo group. A 50% reduction in this rate is considered to be clinically relevant. Hence, in the active treatment group the mean exacerbation rate is set at 1.5 per subject per year. With 33 subjects per treatment group followed up for 1 year, this reduction is detectable with 90% power, given a test size alpha of 0.05 (2-sided).

However, the assumption of a pure Poisson distribution may be too strong. In fact, it is plausible that in this case a zero-inflated Poisson process may be present (the outcome of zero exacerbations has a higher probability than that following from a pure Poisson distribution). In addition there is a risk of overdispersion (the variance is larger than the mean). These phenomena may be expected to have a negative (not exactly quantifiable though) effect on the power of the study.

In order to reasonably compensate for the risk of a too low power and for subjects dropping out within one year follow-up, the number of subjects will be augmented by 40%, so that the sample size is set at 46 subjects per treatment group.

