### Statistical analysis

The exacerbation rate (primary efficacy outcome) will be analysed using Poisson regression, with a log link function and the log of the time-under-treatment as offset. The exacerbation rate ratio of active relatively to placebo treatment will be the efficacy parameter of interest that will be tested for significance at the 5% level (2-sided). In addition a 95% confidence interval of this parameter will be calculated. The following baseline covariates will be entered along with treatment group: steroid maintenance therapy, the number of exacerbations in the year preceding randomisation, age, sex, smoking, and the GOLD criteria (Tiffeneau index and FEV1% of predicted). In order to generate hypotheses concerning the modification of the treatment effect by the steroid therapy, the treatment-by-steroid interaction term will be added to the model and its effect will be explored. When necessary, the scale parameter will be used to correct the SEs for overdispersion. Additionally, a zero-inflated Poisson distribution will be fitted to the data in order to test if a better fit is obtained.

Other continuous (secondary) outcome variables with measurements at baseline, 3, 6, 9 and 12 months will be analysed using mixed model ANOVA. The following covariates will be entered in the model along with treatment group: the baseline measurement of the outcome variable, age, sex, smoking and the GOLD criteria. When appropriate, the outcome variables will be suitably transformed in order to obtain normally distributed residuals.

Time to first exacerbation will be analysed using Cox proportional hazards regression with the following covariates entered in the model along with treatment group: age, sex, smoking and the GOLD criteria. Also a Kaplan-Meier curve for time to first exacerbation per treatment group will be presented for illustrative purposes.

Concerning safety, the number and type of adverse event will be compared between the two treatment groups using the chi square (or Fisher’s exact) test.

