### Ethical aspects

The study has been approved by the ethics committee Toetsingscommissie Wetenschappelijk Onderzoek Rotterdam (TWOR), the ethics committee of the Amphia Hospital Breda and the Centrale Commissie Mensgebonden Onderzoek (CCMO).

The research will be explained in detail (verbally and in writing) to the patient prior to enrolment in the study. The explanation will include the type and method of the research, the tests to be performed, and any potential hazards. An informed consent in writing will be obtained from each patient. The patient can withdraw from the study at any time, without any repercussion for the ongoing care.

The study will be conducted according to the International Conference for Harmonization (ICH) principles of Good Clinical Practice (GCP) and the Declaration of Tokyo (2004). The investigator will conduct all aspects of this study in accordance with all national and regional laws of the pertinent regulatory authorities.

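### The adverse-event comparison makes no allowance for unequal observation time, so total counts and later or other event types can be biased in either direction

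*Protocol article*

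**What the plan says.** The Statistical analysis section gives safety one sentence: "the number and type of adverse event will be compared between the two treatment groups using the chi square" or Fisher's exact test. It names no denominator other than the treatment groups and does not say whether patients or events are counted.

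Adverse events are listed under Secondary study outcome. On capture, that section says: "Symptoms that are believed to be (possibly) related to therapy will be reviewed at the outpatient department". For an event judged drug related it adds: "that does not resolve, then the patient will be withdrawn from the study". The patient therefore leaves the study and does not merely stop treatment. The article does not say whether events are recorded afterwards.

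Three other places bear on observation time:

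- Intervention sets the same planned period for both arms: "Subjects will be randomised to receive either azithromycin 500 mg three times a week or placebo during a 1-year period".
- Two passages foresee early exit in either arm. Ethical aspects says "The patient can withdraw from the study at any time", and the sample size is raised partly "for subjects dropping out within one year follow-up".
- The exacerbation rate is modelled by Poisson regression "with a log link function and the log of the time-under-treatment as offset", and time to first exacerbation by Cox regression. Unequal time is thus allowed for in efficacy but not in the safety sentence.

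**The concern.** A patient who leaves at month 3 has a quarter of the planned year in which to report events. If the arms lose time unequally and collection stops at exit, a raw comparison cannot separate fewer events from less time watched. One route out of this study is toxicity itself, so the loss of time may well differ by arm.

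What is at stake is the safety comparison for a listed secondary outcome, and only part of it: total numbers of events, repeat events, and event types other than the one that led to withdrawal. A real excess of such an event could shrink toward no difference or, if placebo loses more time, look larger than it is.

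**Working it through.** The document gives no adverse-event rate, no withdrawal rate by arm and no figure for the safety comparison, so there is no stated result to reproduce. Two inputs come from it: 46 patients per arm (33 × 1.4 = 46.2) and a planned year of observation. Everything else below is assumed, including that collection stops at withdrawal.

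**Step 1: which quantities move.** Let drug-related events D have hazard hD per year, with a share q of them ending observation, so the exit hazard is c = q·hD. Let another event type O have hazard hO. Over one year:

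- mean observation = (1 − e^(−c))/c
- P(any D) = 1 − e^(−hD)
- P(any event) = 1 − e^(−(hD+hO))
- P(O seen) = hO/(hO+c) × (1 − e^(−(hO+c)))
- expected number of O events = hO × mean observation

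Assumed values: hD 0.4 or 0.8 on active and 0.1 on placebo; hO 0.6 on active and 0.3 on placebo; q from 25% to 100%.

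Neither P(any D) nor P(any event) contains c. With hD = 0.4 on active, the risk difference for any D is 0.330 − 0.095 = 0.235, and for any event 0.632 − 0.330 = 0.302, with or without the rule. With hD = 0.8 they are 0.456 and 0.424, again unchanged. The triggering event is counted before the patient leaves.

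Type O does move. Power is the two-proportion normal approximation, 46 per arm, two-sided 5%.

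| Active hD | q | Mean years, active / placebo | Risk ratio for O | Count ratio for O | Power |
|---|---|---|---|---|---|
| any | 0 (full follow-up) | 1 / 1 | 1.741 | 2.000 | 0.485 |
| 0.4 | 25% | 0.952 / 0.988 | 1.685 | 1.927 | 0.424 |
| 0.4 | 50% | 0.906 / 0.975 | 1.632 | 1.858 | 0.368 |
| 0.4 | 100% | 0.824 / 0.952 | 1.534 | 1.732 | 0.274 |
| 0.8 | 25% | 0.906 / 0.988 | 1.612 | 1.835 | 0.355 |
| 0.8 | 50% | 0.824 / 0.975 | 1.498 | 1.690 | 0.253 |
| 0.8 | 100% | 0.688 / 0.952 | 1.306 | 1.447 | 0.123 |

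Dividing each count by its person-time returns 2.0 in every row.

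**Step 2: direction.** Take the first scenario (hD = 0.4, q = 25%) and let placebo patients also leave for other reasons at an assumed hazard of 0.4 per year. Placebo is then observed for 0.815 years against 0.952 on active. The risk ratio for O becomes 0.4315/0.2134 = 2.02 against 1.74 with full follow-up, and the count ratio 2 × 0.952/0.815 = 2.34 against 2.00. The bias has reversed. The any-event difference also moves here, from 0.302 to 0.357, because this dropout is not itself a counted event.

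**Step 3: size at plainer withdrawal patterns.** If a share w leaves at month m, exposure per patient is 1 − w(12 − m)/12. The apparent count ratio is the true ratio times active exposure over placebo exposure. For an event unrelated to withdrawal, with hazard h = 0.3 per year in both arms, P(at least one) = (1 − w)(1 − e^(−h)) + w(1 − e^(−hm/12)).

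| Withdrawn, active / placebo | Exposure ratio | True 1.30 appears as | Ratio of patient proportions (true 1) | Shift in proportion, × 46 |
|---|---|---|---|---|
| 10% / 3%, month 3 | 0.925/0.978 = 0.95 | 1.23 | 0.95 | 0.013, 0.6 patients |
| 15% / 5%, month 3 | 0.888/0.963 = 0.92 | 1.20 | 0.93 | 0.019, 0.9 patients |
| 20% / 5%, month 2 | 0.833/0.958 = 0.87 | 1.13 | 0.87 | 0.032, 1.5 patients |
| 25% / 5%, month 2 | 0.792/0.958 = 0.83 | 1.07 | 0.83 | 0.042, 1.9 patients |

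For scale, the standard error of a difference in proportions near 0.25 with 46 per arm is √(2 × 0.25 × 0.75/46) = 0.09. Five of 46 patients leaving at mid-year costs 2.5/46, about 5% of person-time.

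**The case against.** The strongest reply is that chi-square or Fisher's test on crude incidence is conventional for a trial of this size, and that exposure-adjusted rates and patient-year columns are details an article leaves to the full protocol or analysis plan. This stands in part. The absence of such tables from the article is no fault. But the article does fix the safety test, and states the withdrawal rule beside it, so whether the two fit can fairly be asked.

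Second, the outcome is framed as events of treatment, so a patient off the drug may contribute little of interest. That bears on whether to collect events after withdrawal. It does not remove the need for a denominator: fewer months on drug still means fewer chances to report an event.

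Third, the shift is below sampling noise at moderate withdrawal: 0.013 to 0.042 against a standard error of 0.09. That stands and limits the weight of the point.

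Fourth, the remedy has limits of its own. Censoring at a withdrawal caused by toxicity may be informative, and the offset assumes a roughly constant event rate; if events cluster early, person-time rates inflate the arm observed for less time. Both limits stand, so the added analyses supplement the patient-level test and do not replace it.

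A reader might infer something stronger: that the arm with more toxicity is necessarily watched for less time and its harm always understated. The document does not support this. Triggering events are already counted, dropout for other causes is foreseen in both arms, and whether collection stops at withdrawal is not settled.

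**Conclusion.** The point holds in a limited form. The stated safety comparison ignores observation time, although the plan itself creates unequal observation and already allows for it in efficacy. If collection ends at withdrawal, total counts and later or other event types can be biased. Under the assumed toxicity-driven withdrawal, a true count ratio of 2.0 appears as 1.45 to 1.93, and a risk ratio of 1.74 for another event type as 1.31 to 1.69. With heavier placebo dropout that risk ratio rises to 2.02.

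The withdrawal rule by itself leaves intact the proportion of patients with any event and the proportion with the triggering event. All these sizes rest on assumed hazards and withdrawal shares, and none can be derived from the document. With few withdrawals the effect is small. This is a worthwhile, inexpensive improvement and not an error that invalidates the safety analysis.

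**What to change.** In the safety paragraph of Statistical analysis:

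- State that the chi-square or Fisher's test counts patients with at least one event, overall and by type. A chi-square test on event counts would treat repeat events in one patient as independent.
- For total events, add a Poisson rate ratio with log observation time as offset, using the scale correction already planned for exacerbations. The offset must be the period over which events were actually counted.
- For the main event types, add a time-to-first-event comparison (log-rank or Cox), with withdrawn patients censored at last contact.
- Report patient-years of observation per arm beside the adverse-event tables.
- Either collect adverse events after treatment stops where the patient agrees, or state that collection ends at withdrawal. The withdrawal rule itself need not change for this.

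The cost is a few lines of text and modest programming, since the model types are already in the plan and onset and exit dates are routine data. Collection after treatment stops would add some follow-up contact. Estimates for rare event types will be imprecise. Because censoring may be informative and the rate may not be constant, the time-based results should be read beside the patient-level proportions.

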### Randomisation

All eligible subjects will be randomised using block randomisation sequences generated by computer. Treatment allocation numbers will be entered into individually sealed opaque envelopes. The envelope contains a number that is concealed to the treatment allocation. The allocation list will be kept in a safe in the hospital pharmacy and access is possible by a non-investigator independently. In the event of an emergency medical situation the individual’s randomisation code and group allocation could be identified.

### Ethical aspects

The study has been approved by the ethics committee Toetsingscommissie Wetenschappelijk Onderzoek Rotterdam (TWOR), the ethics committee of the Amphia Hospital Breda and the Centrale Commissie Mensgebonden Onderzoek (CCMO).

The research will be explained in detail (verbally and in writing) to the patient prior to enrolment in the study. The explanation will include the type and method of the research, the tests to be performed, and any potential hazards. An informed consent in writing will be obtained from each patient. The patient can withdraw from the study at any time, without any repercussion for the ongoing care.

The study will be conducted according to the International Conference for Harmonization (ICH) principles of Good Clinical Practice (GCP) and the Declaration of Tokyo (2004). The investigator will conduct all aspects of this study in accordance with all national and regional laws of the pertinent regulatory authorities.

## Discussion

Despite the clinical efficacy of long-term macrolide treatment in a number of respiratory diseases, until recently, only smaller studies had reported on this subject in patients with COPD. These studies showed conflicting results. One study did examine the effect of clarithromycin treatment in a prospective double-blind randomised controlled trial including 67 patients with moderately severe COPD [22]. The effects of 3 months’ clarithromycin therapy on health status, exacerbation rate and sputum bacterial numbers were measured. No significant benefit was seen except for significant improvements in both the St George’s Respiratory Questionnaire symptom score and 36-item short-form health survey physical function score. Another study investigated the influence of erythromycin treatment on exacerbation of COPD [24]. The total number of patients needed for inclusion was not reached; therefore the study was underpowered. However, the data suggested a beneficial effect in number of exacerbations. Recently Albert et al. [23] showed in a large randomised controlled trial that adding daily 250 mg azithromycin to standard therapy reduced the number of exacerbations in patients with COPD. The major concern with this study, raised in a number of comments and editorials, was the question about the development of antimicrobial resistance, which had almost doubled in that trial [40]. Also the question about the working mechanism of azithromycin, whether it has an antimicrobial or immunomodulatory effect, was not answered in that trial.

With the current study we investigate whether long-term therapy with macrolide antibiotics can prevent exacerbations in patients with an instable COPD. Additionally, our study aims to assess the effect of long-term use of macrolides on the development of antimicrobial resistance and on inflammatory parameters related to COPD. We believe this study will provide more data on the effects of macrolide treatment in patients in COPD and will add more knowledge on its working mechanisms.

## Trial status

The trial is currently recruiting study subjects.

## Abbreviations

COLUMBUS: influence of macrolides on exacerbation frequency in patients; COPD: chronic obstructive pulmonary disease; GOLD: The Global initiative for chronic Obstructive Lung Disease; FEV1: forced expiratory volume in 1 s; FVC: forced vital capacity; HADS: Hospital Anxiety Depression Scale; SF-12: 12-Item Short Form Health Survey; SGRQ: St. George’s Respiratory Questionnaire; PCR: polymerase chain reaction; TWOR: Toetsingscommissie Wetenschappelijk Onderzoek Rotterdam; CCMO: Centrale Commissie Mensgebonden Onderzoek; ICH: International Conference for Harmonization; GCP: good clinical practice.
